## **13. Suspension and Dropout Procedures**

### **A. Clinical Trial Suspension Criteria**

- The clinical trial will be suspended in the following cases.

1. When a patient or their caregiver wishes to discontinue the HBMC intervention
2. When a participant passes away
3. When a participant is hospitalized at a medical institution for an additional four weeks
4. When a patient's treatment at the hemato-oncology department of the respective hospital has been terminated or follow-up has been discontinued
5. When a participant uses an inpatient or home-based hospice care services
6. When the suspension of participation in the clinical trial is deemed best for the participant at the investigator's discretion
7. When a participant does not cooperate with the physician in charge of the clinical trial or does not follow the physician's instructions
8. When the regulatory authority, ethics committee, or Institutional Review Board (IRB) suspends the clinical trial

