|                    | 
discontinued
 
 
5. When a participant uses an inpatient or home-based hospice care services
 
6. When the suspension of participation in the clinical trial is deemed best for the participant at the investigator's discretion
 
7. When a participant does not cooperate with the physician in charge of the clinical trial or does not follow the physician's instructions
 
8. When the regulatory authority, ethics committee, or Institutional Review Board suspends the clinical trial
 
 
* The termination of the study for patients who discontinue the study is as follows.
 
 
- Reasons 1, 3, 4, 5, 6, 7, or 8: Continuation of the investigation of medical records and secondary linkage data (18 months) until 12 months after the enrollment or withdrawal of consent; the additional survey will be conducted only with the patient's consent
 
- Reason 2: Survey or investigation of medical records will not be possible until 12 months after the enrollment; secondary data linkage will be conducted
 
 
* When participation consent is withdrawn, the previously collected data of the patient will be discarded if the patient does not wish the data to be used in the study.
                                                                                                                                                                                                                                                                                                                                                                                                                                                        |

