#### *2) Secondary Efficacy Endpoint*

- Domain 1: The secondary endpoints related to patients' use of medical services and critical care are described below.
  - Number of unscheduled hospitalizations within 6 months of study enrollment (continuous or count variable)
  - Length of hospitalization (total length of hospitalization; continuous variable)
  - History of hospitalization (dichotomous variable)
  - Number of ER visits (continuous variable)
  - Length of ICU hospitalization (total length of hospitalization; continuous variable)
- Domain 2: The secondary endpoints related to patients' quality of life and their satisfaction with the service are described below.
  - Patient's quality of life (EQ-5D; continuous variable)
  - Patient's degree of symptom control (ESAS; continuous variable)
  - Patient's emotional status (PHQ-9; continuous variable)

- Patient's satisfaction with the service (continuous variable)
  
- Domain 3: The secondary endpoints related to the patient's death and preparation of advanced directives are described below.
  - Survival after enrollment (days; continuous variable)
  - Length of ICU hospitalization within 1 month of the patient's death (total length of hospitalization; continuous variable)
  - History of anti-cancer treatment within 1 month of the patient's death (dichotomous variable)
  - Duration of ventilator support within 1 month of the patient's death (total number of days; continuous variable)
  - Preparation of advance directives or physician orders for life-sustaining treatment (dichotomous variable)
  
- Domain 4: The secondary endpoints related to guardians' quality of life and their satisfaction with the service are described below.
  - Guardian's quality of life (EQ-5D; continuous variable)
  - Guardian's emotional status (PHQ-9; continuous variable)
  - Guardian's burden of care (CRA\_K; continuous variable)
  - Guardian's care competency (continuous variable)
  - Guardian's satisfaction with the service (continuous variable)
  
- Domain 5: The secondary endpoints related to medical expenses are described below.
  - Direct medical expenses (continuous variable; KRW)
  - Indirect medical expenses (continuous variable; KRW)

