## **B. Clinical Trial Suspension Procedures**

- A suspension of participation in the HBMC intervention group cannot be resumed.
- Once the suspension of participation in the clinical trial has been decided, the participants (i.e., the patient and guardian) will be asked whether they agree to proceed with the additional survey, except when the suspension is due to death.

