## **C. Follow-up of Suspended Participants**

- Investigation of the medical records and secondary data linkage will be performed on the suspended participants from the time of suspension to the end of the remaining scheduled follow-up period (18 months after the registration) until no longer possible due to the participant's death, failure to follow-up, or withdrawal of consent. Any case of a patient receiving additional HBMC services (e.g., other HBMC pilot projects) other than the one provided in this clinical trial after the completion of the study will be recorded in the care

reports.

- For participants suspended due to reasons other than death, the follow-up survey will only be conducted with those who consent to participate via a telephone call made by a research nurse.

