### ***4) Statistical analysis***

Definition of home-based medical service intervention group and study dropouts: Patients who provided informed consent to the selected home-based medical service intervention institutions and control group institutions are defined as the intervention group and control group, respectively. Based on the principle of group classification by intention-to-treat (ITT) that only considers the initial classification of intervention, omission of home-based medical service is still defined as the intervention group, which causes a bias that reduces the effects in the treatment group. Despite the study's design to conservatively estimate the effects in the treatment group, if significant differences are observed in the results among patients who withdraw consent or dropout during follow-up, data up to the point of withdrawal of consent or dropout will be used. Dropout rates will be analyzed and reported for each group.

The mean proportion of unplanned hospitalization will be compared between the intervention and control groups for the primary outcome. The mean of continuous variables and a fraction of dichotomous variables for each item in domains one to five will be compared between the two groups for the secondary outcome. A generalized estimation equation will be used to evaluate intra-group correlations to compensate for clusters of patients in the participating institutions. Survival after enrollment will be compared using the Kaplan-Meier curve and Cox proportional hazard model.

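### Stopping HBMC suspends the pair from the trial and makes its later questionnaires depend on fresh agreement; only the HBMC arm can meet this trigger, so 3-month questionnaire data can be lost one-sidedly

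*Protocol*

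**What the plan says.** Section 13.A opens with "The clinical trial will be suspended in the following cases", and its first criterion is "When a patient or their caregiver wishes to discontinue the HBMC intervention". The Suspension Criteria row of the Overview repeats it. Other criteria on the list, such as "When a participant uses an inpatient or home-based hospice care services", can be met in either arm.

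After suspension for any reason but death, section 13.B says that "the participants (i.e., the patient and guardian) will be asked whether they agree to proceed with the additional survey". It adds that suspension in the HBMC group cannot be reversed. Section 13.C says that "the follow-up survey will only be conducted with those who consent to participate via a telephone call made by a research nurse". The Overview words the condition differently: "the additional survey will be conducted only with the patient's consent". Chart review and secondary linkage continue after suspension (Overview; section 13.C).

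On analysis, section 14.B.4 follows intention to treat, so that "omission of home-based medical service is still defined as the intervention group". For withdrawals and dropouts, that section and the Statistical Analysis row of the Overview use the data gathered up to that point.

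The questionnaire outcomes are secondary endpoints in section 12.A.2: patient EQ-5D, ESAS and PHQ-9 in Domain 2, and guardian EQ-5D, PHQ-9 and CRA-K in Domain 4.

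**The concern.** Stopping an intervention and leaving a trial are different events, and an intention-to-treat comparison needs follow-up to continue after the first. Here the first sets off a step that puts questionnaire follow-up at risk. Section 13.D points the same way, because it describes taking part as receiving HBMC and being evaluated, together.

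Criterion 1 exists in practice in one arm only. A caregiver who finds home care too heavy, and so asks to stop HBMC, must agree again before the next questionnaire. A control caregiver under the same strain has no HBMC to stop and does not meet this criterion. If stopping is related to burden, low mood or symptoms, the missing values are informative, and assigning the pair to its original group cannot replace answers that were not obtained.

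Two features of the plan add weight. The Overview marks safety assessment as not applicable, so these scales are the main place where strain from care at home could show. Section 12.C.2 reads a difference at the 0.05 level on a secondary endpoint as evidence that HBMC works.

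**Working it through.** The plan states no figure on this point, so there is none to reproduce. The check is a reading of the rules, followed by an illustration of size.

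**Who can be affected, and when**

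- *Trigger.* Criterion 1 can be met only by pairs receiving HBMC. Under the Control heading, control patients get educational materials and usual oncology care. Criteria 2 to 8 are not specific to an arm.
- *Consequence.* The renewed request for agreement follows criteria 1 and 3 to 8 in whichever arm they occur. Only the criterion 1 trigger is one-sided.
- *Outcomes.* Records and linkage continue, so hospital-use outcomes, including the primary endpoint, do not depend on survey agreement. Only questionnaires do.
- *Time point.* At 3 months the Overview, the text of section 11.A and its schedule table all put these scales in both arms. At 6 months they disagree. The text of 11.A surveys both groups. The Overview surveys only controls who gave extra consent at 3 months. The table marks these scales as intervention-only, and attaches the extra-consent footnote only to caregiver indirect expenses. The 3-month comparison is therefore the one clearly at stake.
- *Whose agreement.* The Overview names the patient, section 13.B the patient and guardian. On the Overview's wording, a caregiver's data could turn on the patient's decision.

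**Size, on assumed rates**

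Let d be the share of HBMC pairs suspended under criterion 1 before the questionnaire, r the share of these who then decline it, and k the excess burden of those who stop over those who stay, in SD. With those who stay set at zero:

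- mean of the whole arm = d·k
- observed mean = d(1−r)k / (1−d·r)
- shift = observed − whole = −d·k·r(1−d) / (1−d·r)
- questionnaires missing = 198·d·r (198 per arm, section 6)

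The protocol gives none of d, r or k. The grid is d = 5–15%, r = 25–100%, k = 0.3–0.8. The 15% is borrowed from the maximum dropout per institution in section 6, which covers any reason in either arm, so it is a generous ceiling for d.

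| d | r | k | Missing of 198 | Shift (SD, favouring HBMC) |
|---|---|---|---|---|
| 5% | 25% | 0.3 | 2.5 | 0.004 |
| 10% | 50% | 0.5 | 9.9 | 0.024 |
| 5% | 100% | 0.5 | 9.9 | 0.025 |
| 15% | 100% | 0.5 | 29.7 | 0.075 |
| 15% | 100% | 0.8 | 29.7 | 0.120 |
| any | any | 0 | 198·d·r | 0 |

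Mid-case: 0.10 × 0.5 × 0.5 × 0.90 / 0.95 = 0.024. If those who stop are less burdened (k below 0), the shift runs against HBMC.

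**Against sampling error**

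Assume that the plan's ICC of 0.015, set for hospitalization, also holds for these scales. With clusters of 66, the design effect is 1 + 65 × 0.015 = 1.975 and the effective number per arm is 198 / 1.975 = 100.3. The standard error of a difference is √(2/100.3) = 0.14 SD. A shift of 0.024 to 0.075 SD is then about 0.2 to 0.5 standard errors.

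**The case against.** The strongest reply is that little is lost. Pairs are asked, those who agree are surveyed by telephone, and under any ethical rule they could decline anyway. Section 14.B.4 governs classification, and nothing in section 13 moves a pair out of its group. Chart review and linkage go on. Dropout is already to be reported by group.

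Much of this stands. There is no conflict over group membership; the tension with intention to treat concerns only the outcomes that need a questionnaire. The practical gap between asking first and letting a pair decline when called may be small. Dropout reporting would show an imbalance, but it would not supply the missing answers.

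A reader might infer more than the protocol supports:

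- *That burden and distress are in fact under-recorded in the HBMC arm.* The rule creates the risk. Whether it materialises depends on how many stop, how many then decline, and whether they differ, and the documents are silent on all three. Pairs may also stop because their need is low.
- *That data are lost from one arm only.* Fresh agreement also follows criteria 3 to 8 in either arm, and a control pair may withdraw at any time under section 13.D.
- *That HBMC has the poorer data throughout.* At 6 months, the Overview and the schedule table restrict the control arm more.
- *That a difference in the proportion of highly burdened caregivers measures the bias.* The plan analyses CRA-K as a continuous score, so such a proportion is not an endpoint.

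**Conclusion.** The point holds as a weakness in the follow-up rule. Criterion 1 ties stopping HBMC to suspension from the trial. Only the HBMC arm can meet it, and it adds a consent step before the 3-month questionnaires, the one follow-up at which every relevant part of the protocol schedules these scales in both arms.

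The likely size is modest: about 0.02 to 0.08 SD when those who stop are 0.5 SD more burdened and 5–15% stop, with refusal between half (at 10% stopping) and complete. The full grid runs from 0.004 to 0.12 SD, and the shift is zero if those who stop do not differ. All rates are assumptions. The primary endpoint and other record-based outcomes are untouched. The change is worth making because it is cheap and because missing questionnaires cannot be recovered at analysis.

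**What to change.** - In the Suspension Criteria row of the Overview and in sections 13.A to 13.C, separate the two events. A pair meeting criterion 1 ends the HBMC intervention only. It stays on the scheduled questionnaires under its original consent, by phone or email as section 11.A already allows, unless it declines a questionnaire or withdraws consent.
- Do not extend this automatically to criterion 6 (suspension judged best for the participant by the investigator) or criterion 8 (suspension by a regulator, ethics committee or IRB). Carrying on with questionnaires by default would not be appropriate there.
- Analyse these questionnaires in the assigned group, and report 3-month completion by arm and by suspension reason.
- Reconcile whose agreement counts after suspension: the patient's (Overview) or the patient's and guardian's (section 13.B).
- Reconcile the 6-month questionnaire schedule between the arms across the Overview, the text of section 11.A, and its table and footnote.

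The cost is protocol and consent wording plus a few extra telephone questionnaires by research nurses already in place. The downside is a slight added questionnaire burden for pairs that have stopped HBMC, who keep the right to decline. The rule on when HBMC stops does not change.

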## **B. Clinical Trial Suspension Procedures**

- A suspension of participation in the HBMC intervention group cannot be resumed.
- Once the suspension of participation in the clinical trial has been decided, the participants (i.e., the patient and guardian) will be asked whether they agree to proceed with the additional survey, except when the suspension is due to death.

## **C. Follow-up of Suspended Participants**

- Investigation of the medical records and secondary data linkage will be performed on the suspended participants from the time of suspension to the end of the remaining scheduled follow-up period (18 months after the registration) until no longer possible due to the participant's death, failure to follow-up, or withdrawal of consent. Any case of a patient receiving additional HBMC services (e.g., other HBMC pilot projects) other than the one provided in this clinical trial after the completion of the study will be recorded in the care

reports.

- For participants suspended due to reasons other than death, the follow-up survey will only be conducted with those who consent to participate via a telephone call made by a research nurse.

#### **D. Participant Dropout Procedures**

- Study participants are free to discontinue participation in the clinical trial (the provision of the HBMC intervention and evaluation) at any time (withdrawal of consent). The reasons for the dropout will always be confirmed with these participants. If possible, the investigator will conduct a participant interview and perform a scheduled post-trial assessment and procedures.
- In the case of dropout patients, their previously collected data will be discarded if they do not wish the data to be used in the study.

## **14. Statistical analysis**

### **A. Hypothesis**

The intervention group will show a 20% decrease in unplanned hospitalization than the control group.

### **B. Outcome variables**

#### ***1) Primary outcome measures***

Unplanned hospitalization within 6 months following enrollment

#### ***2) Secondary outcome measures***

Patients' medical service utilization, hospitalization, ER visits, healthcare use, end-of-life care (intensive care unit admission, ventilator treatment, and an advance directive), quality of life (modified Edmonton Symptom Assessment System [ESAS] and Euro-Quality of Life-5 Dimension [EQ-5D]), depressive symptom (patient health questionnaire-9 [PHQ-9]), caregivers'

quality of life and satisfaction with the services, and medical expenses.

### ***3) Study group***

Intervention and control groups

### ***4) Statistical analysis***

Definition of home-based medical service intervention group and study dropouts: Patients who provided informed consent to the selected home-based medical service intervention institutions and control group institutions are defined as the intervention group and control group, respectively. Based on the principle of group classification by intention-to-treat (ITT) that only considers the initial classification of intervention, omission of home-based medical service is still defined as the intervention group, which causes a bias that reduces the effects in the treatment group. Despite the study's design to conservatively estimate the effects in the treatment group, if significant differences are observed in the results among patients who withdraw consent or dropout during follow-up, data up to the point of withdrawal of consent or dropout will be used. Dropout rates will be analyzed and reported for each group.

The mean proportion of unplanned hospitalization will be compared between the intervention and control groups for the primary outcome. The mean of continuous variables and a fraction of dichotomous variables for each item in domains one to five will be compared between the two groups for the secondary outcome. A generalized estimation equation will be used to evaluate intra-group correlations to compensate for clusters of patients in the participating institutions. Survival after enrollment will be compared using the Kaplan-Meier curve and Cox proportional hazard model.

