| Statistical Analysis         | 
The HBMC intervention group, control group, and each participating institution will be set as analysis groups for the statistical analysis of the outcome variables.
 
The analysis groups of the participants are based on the group assignment according to the initial intention-to-treat (ITT) that relies solely on the intervention of the original assignment to estimate the effectiveness in the intervention group conservatively. In the case of withdrawal of consent or dropout during follow-up, data collected till the time of withdrawal or dropout will be used. A comparative analysis of the dropout rate between the two groups will be performed and reported.
 
 
- Descriptive analysis of underlying characteristics
 
 
Continuous variables: mean (standard deviation) and median (IQR)
 
Dichotomous variables: frequency (%)
 
 
- Analysis of between-group differences
 
 
An analysis will be performed using a regression model while considering that participants, the observation units, were clustered into six participating institutions to evaluate the effects of the HBMC intervention and correcting for the differences in the baseline characteristics between the groups.
 
Dichotomous variable (primary endpoint): A generalized estimation equation (GEE) will be used to analyze the clusters of patients in participating institutions, and the effects of the HBMC intervention will be evaluated using a logistic regression model based on the logit link function.
 
Continuous variables: The effects of the HBMC intervention will be evaluated using a mixed model to consider the patient clusters in the participating institutions.
 
Count data: A GEE will be used to consider the patient clusters in the participating institutions, and the effects of the HBMC intervention will be evaluated using a regression model that appropriately uses Poisson and negative binomial as random components according to the distribution of variables using the logit link function as the link function.
 |

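### Section 14.B.4 ties the use of withdrawn or dropped-out patients' data to significant differences in the results, while the protocol overview uses the same data unconditionally

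*Protocol*

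**What the plan says.** Section 14.B.4 sets the analysis principle: "Based on the principle of group classification by intention-to-treat (ITT) that only considers the initial classification of intervention". A patient at an intervention institution who receives no HBMC therefore stays in the intervention group. After a remark that the design is conservative, it says that "if significant differences are observed in the results among patients who withdraw consent or dropout during follow-up, data up to the point of withdrawal" or dropout will be used. The same subsection fixes the primary comparison: "The mean proportion of unplanned hospitalization will be compared between the intervention and control groups for the primary outcome".

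The Statistical Analysis row of the overview covers the same patients without a condition: "In the case of withdrawal of consent or dropout during follow-up, data collected till the time of withdrawal or dropout will be used".

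Two further rules apply, and neither depends on results:

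- **Discard at the patient's wish.** On withdrawal of consent, the overview (Suspension Criteria row) says that "the previously collected data of the patient will be discarded if the patient does not wish the data to be used in the study". Section 13.D says the same for dropouts.
- **Suspension.** Section 13.C says: "Investigation of the medical records and secondary data linkage will be performed on the suspended participants from the time of suspension". This runs to 18 months after registration, unless death, failure of follow-up or withdrawal of consent ends it sooner.

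**The concern.** Which patients and which data enter the primary analysis should be settled without reference to the outcome. Section 14.B.4 makes part of that choice follow a significant difference, and leaves open which difference, which test and level, and what happens when the condition is not met. An analyst could include or omit the partial data after seeing the results and claim support from the protocol either way.

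This goes beyond detail that could be left to a statistical analysis plan. The protocol states two rules that disagree. A plan that follows Section 14 takes over the condition, and one that follows the overview departs from Section 14. The trial is non-randomised with three institutions per group, so pre-specification is one of its few safeguards.

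**Working it through.** **1. The two rules side by side**

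| | Section 14.B.4 | Overview, Statistical Analysis |
|---|---|---|
| Patients | withdrew consent or dropped out | the same |
| Data | up to withdrawal or dropout | the same |
| Condition | significant differences in the results | none |
| Result, test and level for the condition | not named | not needed |
| If the condition is not met | not stated | does not arise |

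The discard rule and Section 13.C do not resolve this. The first acts on the patient's wish, and the second concerns suspended patients.

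**2. How many patients are concerned**

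Inputs from Section 6: 66 patients in each of 6 institutions (396), a maximum dropout of 15%, and 57 per institution (342) after dropout.

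- By the plan's own figures: 66 − 57 = 9 per institution, and 6 × 9 = 396 − 342 = 54 patients.
- Unrounded: 0.15 × 396 = 59.4 patients.

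The range is therefore about 54 to 59 of 396, or 27 to 30 per group if spread evenly.

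**3. What the condition could do to the type I error**

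The protocol gives no figure, so this is an illustration. From the protocol: 198 per group and 15% dropout. Assumed: 30% dropout as a second case, true event rates of 0.3 or 0.5 in both groups, half the event risk observed before dropout, no clustering, and a two-sided pooled z-test at 0.05. There were 200,000 simulated trials per row, so the Monte Carlo standard error is about √(0.05 × 0.95 / 200,000) = 0.0005.

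The conditional rule was taken to mean: add the partial data if the dropouts' results differ significantly between groups, otherwise analyse completers only.

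| Event rate | Dropout | Completers only | Partial data always used | Conditional rule | Whichever set is significant |
|---|---|---|---|---|---|
| 0.3 | 15% | 0.051 | 0.048 | 0.053 | 0.064 |
| 0.3 | 30% | 0.051 | 0.046 | 0.055 | 0.069 |
| 0.5 | 15% | 0.056 | 0.045 | 0.058 | 0.067 |
| 0.5 | 30% | 0.047 | 0.042 | 0.053 | 0.065 |

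The conditional rule gives 0.053 to 0.058. The last column, 0.064 to 0.069, requires a free choice of the favourable data set, which Section 14.B.4 does not grant.

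**The case against.** The strongest reply is that the sentence is a drafting accident. Section 14.B.4 and the overview run in the same order: intention-to-treat by initial assignment, conservative estimation, data up to withdrawal or dropout, comparison of dropout rates. The extra clause could be a remark that a significant result despite a conservative design is persuasive, run together in translation with the data rule that follows. The authors may well have meant the overview's rule. That is plausible and limits what can be said about intent, but the text as it stands does not say it.

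A reader might infer four stronger claims that the documents do not support:

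- **Partial data are used only if results differ.** The protocol says if, not only if. The exclusive reading is an inference: without it the clause does nothing, but the alternative is never stated.
- **The nominal 5% level is invalidated.** The illustration shows modest inflation under the conditional rule.
- **Hospice use, long hospital stays or the end of oncology treatment cause informative truncation.** Section 13.A lists these as reasons for suspension, and Section 13.C keeps collecting those patients' records. Dropout is a separate procedure in Section 13.D, identified there with withdrawal of consent. What stands is that the boundary is blurred: wishing to stop HBMC is a suspension reason, while Section 13.D describes dropout as stopping both HBMC and evaluation.
- **The rule shifts the group difference by some 2 points.** With a constant hazard and dropout uniform over 6 months, a truncated patient shows an event with probability 1 + p/ln(1 − p), where p is the 6-month event rate. For p = 0.50 this is 0.279, and dropout of 20% against 10% shifts the difference by 0.10 × (0.50 − 0.279) = 2.2 points. But 20% exceeds the protocol's 15% maximum, and the 50% rate is not in the protocol. With p = 0.20, close to the 40 of 198 in Section 6, the probability is 0.104 and the shift 0.10 × (0.20 − 0.104) = 1.0 point. Either shift measures truncation and would arise equally under the overview's unconditional rule.

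**Conclusion.** The protocol is wrong as written. It contains two incompatible rules for the same patients. The one in the section that governs the analysis depends on results, is incompletely defined and conflicts with the stated intention-to-treat principle. This conclusion rests on the text alone.

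The data at issue belong to about 54 to 59 of 396 patients if dropout reaches the 15% maximum, and to fewer if it does not. The effect on type I error is probably small, but the figures rest on assumed event rates, partial follow-up and trigger, and they ignore clustering by institution. The documents do not show that the sponsor intends to select data on results. The main fault is an undefined, results-dependent analysis set and a contradiction, which should be removed before outcomes are analysed.

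**What to change.** Delete the conditional clause in Section 14.B.4 and put one rule there and in the overview. In substance:

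- All enrolled patients are analysed in the group of their institution, using data collected up to withdrawal of consent or dropout, whatever the results show. The only exception is a patient's request to have earlier data discarded (overview, Suspension Criteria row; Section 13.D).
- Suspension of HBMC is not dropout. Record-review data collected after suspension under Section 13.C count toward the 6-month primary endpoint in both groups.
- Linkage data are used for that endpoint only once the overview's Efficacy Assessment row, which describes linkage for consenting patients without limiting it to a group, is reconciled with Section 11.C, which describes it for the intervention group. Otherwise the groups could be ascertained differently.

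The first two items cost a wording amendment and its IRB approval. Record review at 3, 6 and 12 months is already planned in Section 11.B. The linkage item may cost more than wording, because linkage rests on a separate consent (Section 9.A.1) and the plan for control patients has to be settled first.
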